### Privacy and informed consent

To ensure privacy of the patients, the participating practices will send the invitation letters to the patients. Additional information in the invitation letter will inform the participants about the study purposes. At the start of the online risk estimation and lifestyle assessment, all patients are asked to complete a digital informed consent form.

We will obtain data on health care utilization of all patients through data extraction from the EMR of the GPs. Based on the Dutch law for data protection, obtaining informed consent for this part of the data collection is not necessary. All obtained data will be processed anonymous, not traceable to individual patients. The study was considered by the UMC Utrecht Institutional Review Board and exempted from full assessment under the Medical Research involving human subjects Act.

## Discussion

This manuscript describes the design of the INTEGRATE study, a study aiming to establish the effectiveness and cost-effectiveness of a Personal Prevention Approach for cardiometabolic risk (PPA CMR) in primary care. An additional aim is to provide more insight into the profile of participants and non-participants and the effectiveness of the various components of the program. Our final goal is to contribute to the reduction of cardiometabolic morbidity and mortality in an aging population.

### Choices in study design

In the design of this study we made a number of choices that need to be addressed:

1. Design

We have chosen a stepped-wedge randomized controlled trial design. Patients will either be allocated to the intervention group or the waiting list control group that starts the intervention after one year. The waiting list control group is necessary to measure ‘natural’ changes in lifestyle among eligible persons and to estimate the number of newly detected CMD without exposure to PPA CMR. At the end of the study PPA CMR is completely implemented in all participating practices and all eligible patients have received the intervention. Implementation of PPA CMR is done in time periods to distribute the workload for the GPs and their staff.

2. Randomization

Participants are not informed about the existence of a waiting list control group and none of the participants will know to which group they are assigned. Nevertheless, the nature of this intervention makes total blinding of the participants impossible. To minimize bias and maximize the validity of the results, both groups will receive the same standardized care, according to the evidence based practice guidelines issued by the Dutch College of GPs. For practical reasons, selection and randomization of all eligible patients will be done at baseline. Randomization is performed at individual level and is done to equally distribute correlating factors of patients registered within the same practice. Because randomization takes place before consenting to participate, selective response can be induced (see ‘possible methodological threats’). Randomization within practices can cause ‘contamination’, lifestyle changes of patients may affect the lifestyle of their spouse and others in their environment. When spouses are assigned to different groups this can influence the results, causing an underestimation of the effectiveness of PPA CMR.

3. Integration in routine primary care

Since PPA CMR is based on a Dutch GP guideline and can be considered ‘standard care’, we have chosen to implement PPA CMR into routine primary care. This way we can evaluate the effects of an existing screening program for patients at risk for CMD combined with tailored treatment for risk factors in the most natural way.

4. Practice characteristics

Lifestyle interventions may differ between general practices. For example, some practices have a lifestyle coach or collaborate with local providers of lifestyle interventions whereas in other practices GPs only give lifestyle advice. Changes in lifestyle are hard to accomplish, especially maintaining a healthy lifestyle asks a lot of perseverance from patients. Intensive support by a lifestyle coach or providing local lifestyle interventions may provide the necessary continuity to achieve a more sustainable reduction in cardiometabolic risk. We will carefully document practice characteristics to evaluate which factors influence compliance with and enhance effectiveness of the program.

5. Modeling

One year of follow up will not be sufficient to fully assess all the costs and benefits of PPA CMR. Improvements in risk profile will only translate in a reduction in cardiometabolic events in the longer term. Modeling is therefore necessary to extrapolate study findings to the longer term. The RIVM-CDM, developed at the National Institute for Public Health and the Environment, has been widely accepted for evaluation of cost-effectiveness, also in other prevention programs [34,36-38]. A disadvantage of modeling is the potentially large effect of small uncertainties of input data on the output of the model. For instance, if the effect of PPA CMR on patients’ risk profiles would decrease after one year, this could result in an overestimation of the long-term effects of the program. Probabilistic sensitivity analysis will be performed to assess the level of uncertainty of model outputs.

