### Endpoints and measurements

The endpoints of the INTEGRATE study are shown in Table 2. An overview of all measurements is shown in Figure 2.

**Table 2 T2:** Primary and secondary endpoints

**Primary endpoints**	**Secondary endpoints**
1. The number of newly detected patients with a CMD in one year follow-up	1. Difference in primary outcome 5 after implementation of different response-enhancing strategies
2. Change in individual risk factors (smoking, physical inactivity, obesity, unhealthy diet, blood pressure and cholesterol levels) for CMD between baseline and one year follow-up	2. Change in willingness to change lifestyle between baseline and one year follow-up
3. The expected number of newly detected patients with CMD and mortality after 5, 10,20 years and lifetime	3. Change in health status between baseline and one year follow up
4. Costs-effectiveness of PPA CMR	
5. Non-participation and compliance in different stages of PPA CMR	

For our secondary endpoints we will use the information provided for our primary endpoints.

1. *Newly detected patients with CMD at baseline and one year follow-up*

The number of newly detected patients with pre-existing CMD will be established after the second consultation and after one year follow-up, based on ICPC-1-coded diagnoses (see Table 1) in the EMRs.

2. *Change in individual risk factors for CMD between baseline and one year follow-up*

For patients with an increased risk for CMD, risk and lifestyle profiles will be established at the start of PPA CMR and after twelve months of follow-up. Risk profiles consist of the completed risk profile including the additional measurements done by the GP or with the self-management toolbox. The questions of the online risk estimation and lifestyle assessment are repeated after six months as well (see Figure 2).

For patients with a low risk for CMD we will establish risk and lifestyle profiles at the start of PPA CMR and after twelve months of follow-up. These risk profiles do not contain the additional measurements.

3. *Expected newly detected patients with CMD and mortality after 5, 10, 20 years and lifetime*

We will use the RIVM-Chronic Disease Model (RIVM-CDM) [28,29] to extrapolate the number of possible prevented CMD due to PPA CMR with a time horizon of 5, 10 and 20 years. The calculations are based on changes in risk profile during one year of treatment.

4. *Costs-effectiveness of PPA CMR*

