#### Cost-effectiveness of PPA CMR

We will perform an economic evaluation to relate net incremental costs and effects of PPA CMR compared to the waiting list control group. Estimated costs are based on the healthcare and non-healthcare costs. After one year of follow-up, cost-effectiveness of PPA CMR will be established. To evaluate cost-effectiveness in the long term, modeling is required. We will use the RIVM-Chronic Disease Model (RIVM-CDM) to perform this long-term economic evaluation. The RIVM-CDM is a Markov-type, dynamic population-based model [28,29] and is able to relate changes in prevalence of risk factors to changes in future incidence of CMD. The model also contains data on costs of cardiovascular events and associated losses in quality of life. This model has extensively been used for the evaluation of cost-effectiveness of prevention programs targeted at lifestyle improvement [34,36-38].

The cost-effectiveness will be calculated per level of change in individual risk factors. Incremental cost-effectiveness ratios (ICER) are derived from calculating the net costs of PPA CMR compared to the waiting list control group, divided by its effect. In addition, we will calculate the incremental cost-utility ratios (ICUR). Therefore, the incremental costs of PPA CMR compared to the waiting list control group will be divided by the effects in quality adjusted life years (QALY’s) gained. Utility values as incorporated in the RIVM-CDM will be used for future cardiovascular events. Probabilistic sensitivity analysis are performed for all calculations.

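### The plan names fading of the one-year effect as a threat to its long-term results but answers it only with probabilistic sensitivity analysis, which helps only if persistence is varied

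*Protocol article*

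**What the plan says.** Table 2 of the protocol article lists as primary endpoint 3 "The expected number of newly detected patients with CMD and mortality after 5, 10,20 years and lifetime". The method text for that endpoint, under Endpoints and measurements, says the RIVM-CDM will be used "to extrapolate the number of possible prevented CMD due to PPA CMR with a time horizon of 5, 10 and 20 years", and gives the input: "The calculations are based on changes in risk profile during one year of treatment". Lifetime appears in the table but not in that method sentence.

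Under Cost-effectiveness of PPA CMR, cost-effectiveness is to be established at one year, and the model is then used for the long term. The model is described in these words: "The RIVM-CDM is a Markov-type, dynamic population-based model". The section ends: "Probabilistic sensitivity analysis are performed for all calculations".

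Under Choices in study design, item 5 (Modeling), the article calls sensitivity to small uncertainties in the input data a drawback of modelling and gives an example: "if the effect of PPA CMR on patients’ risk profiles would decrease after one year, this could result in an overestimation of the long-term effects". The next sentence is the whole response: "Probabilistic sensitivity analysis will be performed to assess the level of uncertainty of model outputs".

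The article does not state a base-case assumption about the effect after year one, a waning scenario, or a list of the parameters that the probabilistic analysis will sample.

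**The concern.** The threat and the remedy are of different kinds. The threat has a direction: if the effect fades and the model carries forward more of it than remains, the benefit is too large. The remedy describes spread. If the analysis samples the size of the one-year effect but leaves its later course alone, it puts an interval around a centre that may be wrong and does not move that centre.

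The article itself gives a reason to take fading seriously. Item 4 of Choices in study design says that keeping up a healthy lifestyle demands much perseverance.

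The trial cannot settle the matter. According to Study design, Randomization and Control group, the waiting list groups start PPA CMR after one year, and the follow-up described under Endpoints and measurements ends at twelve months. Any statement about years 2 to 20 is therefore an assumption and should be visible as one.

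At stake are primary endpoint 3 and the long-term part of primary endpoint 4. The Conclusion says that favourable results would form the evidence base for national prevention programmes. A long-term cost-effectiveness result could look robust only because persistence was never varied.

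**Working it through.** **The plan's own figures.** The article gives no waning rate, no list of sampled inputs and no model result, so there is no long-term figure to reproduce. The illustration borrows its scale from Sample size calculation: smoking falling from 25% to 20% with controls stable, 721 intervention patients, ratio 1:4. The 721 does reproduce, with the continuity-corrected two-proportion formula at two-sided alpha 0.05 and 80% power (696 without the correction). The point does not depend on it.

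**Step 1: how much persistence matters.** Assume a constant proportional loss d per year after year one.

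- Effect-years over T years, per unit of one-year effect: S = sum over k = 0 to T−1 of (1−d)^k = (1 − (1−d)^T)/d
- Under full persistence: T
- Overstatement if full persistence is assumed: T/S

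| Assumed d | 5 years | 10 years | 20 years |
|---|---|---|---|
| 0% | 5/5 = 1.0 | 10/10 = 1.0 | 20/20 = 1.0 |
| 5% | 5/4.52 = 1.11 | 10/8.03 = 1.25 | 20/12.83 = 1.56 |
| 10% | 5/4.10 = 1.22 | 10/6.51 = 1.54 | 20/8.78 = 2.28 |
| 20% | 5/3.36 = 1.49 | 10/4.46 = 2.24 | 20/4.94 = 4.05 |
| 50% | 5/1.94 = 2.58 | 10/2.00 = 5.0 | 20/2.00 = 10.0 |

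Every rate here is an assumption. The effect-years are undiscounted, and this is not the RIVM-CDM.

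**Step 2: what a probabilistic analysis does with it.** Take a one-year effect of 0.05. Its standard error, ignoring clustering, is √(0.20 × 0.80/721 + 0.25 × 0.75/2884) = 0.0169. With 200,000 draws, compare two versions: one samples only the one-year effect, the other also samples d uniformly from 0 to 0.30. The reference is the value under 20% annual waning, 0.05 × S.

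| Horizon | Persistence fixed: mean (95% interval) | Waning sampled: mean (95% interval) | Value at 20% waning |
|---|---|---|---|
| 5 years | 0.25 (0.08 to 0.42) | 0.19 (0.06 to 0.34) | 0.17 |
| 10 years | 0.50 (0.17 to 0.83) | 0.29 (0.08 to 0.62) | 0.22 |
| 20 years | 1.00 (0.34 to 1.66) | 0.40 (0.09 to 1.11) | 0.25 |

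With persistence fixed, the mean stays at the full-persistence value at every horizon. At 5 and 10 years the interval still covers the waned value, because the one-year effect is itself imprecise. At 20 years it does not: 0.25 lies below 0.34. Once waning is sampled, the mean moves and the interval covers the waned value at all three horizons.

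**Step 3: what follows for the plan.** Whether the probabilistic analysis addresses the named threat depends on one choice, namely whether persistence after year one is varied. The article does not make that choice.

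**The case against.** The strongest case against the point is that the article nowhere says the effect is held constant after year one. The sentence on one-year changes names the input and not the later trajectory, and the model is called dynamic, with its workings left to references. Fading is introduced as an instance of input uncertainty, which is what a probabilistic analysis samples, and a decay rate could be among the sampled parameters. A journal article may also leave the parameter list and the scenario runs to a fuller economic plan.

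Much of this stands, and it rules out stronger readings that a reader might infer:

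- That the long-term results will be overestimated. The article's statement is conditional: only if the effect decreases does it say "this could result in an overestimation of the long-term effects of the program". With no waning there is no bias from this source.
- That the probabilistic analysis certainly leaves persistence untested. Its inputs are not listed, so this cannot be said.
- That cost-effectiveness as a whole is compromised. The one-year evaluation does not use the extrapolation.
- That the benefit is overstated fourfold and the ICER is off by the same factor. Fourfold belongs to one assumed rate at one horizon. The model also contains costs of cardiovascular events, so net costs would change with the effect.

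The objection does not remove the point. The warning makes sense only if the calculation could carry forward more effect than truly remains, so some persistence is implied. The complaint is also not that details are unlisted: the article names a bias in its own primary endpoint and pairs it with a method that does not by itself address that bias.

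**Conclusion.** The point holds in a conditional form. The plan's only stated answer to fading is a method that reveals it only if persistence after year one is itself varied, and the trial has no randomised contrast beyond 12 months to inform that persistence. Primary endpoint 3 and the long-term part of endpoint 4 may therefore be overestimated.

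The size cannot be taken from the document. Over assumed waning of 0% to 50% a year, the overstatement of effect-years under full persistence runs from none to about 2.6 times at 5 years and 10 times at 20 years. Discounting would shrink these factors, because the later years carry the largest gap. The effect on the ICER also depends on modelled cost offsets. Confidence is high that threat and remedy do not match as written, and low on how large any bias would be.

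**What to change.** Keep the probabilistic analysis and make three additions to the economic analysis plan.

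1. State what the base case assumes about the effect after year one.
2. Pre-specify scenarios at each horizon: effect maintained; effect declining by a fixed share per year (10% and 20%, for example); full return to the control trajectory after year one. Alternatively, sample a decay rate in the probabilistic analysis, from a distribution that allows substantial waning and is declared as an assumption.
3. Report modelled CMD and mortality, the ICER and the ICUR for each scenario beside the base case.

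Also make the list of horizons agree, since lifetime stands in Table 2 but not in the method sentence, and run the scenarios for every horizon that is kept.

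The cost is a few extra model runs and a short addition to the text, with no new data. The price is that the headline long-term cost-effectiveness becomes a range, which may look less favourable.

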### Non-response analyses

The results of the non-response analyses of the INTEGRATE study will provide more information about the characteristics and motives of non-participants in PPA CMR. This knowledge is relevant and essential for the development and evaluation of participation enhancing strategies. The INTEGRATE study has a unique design where the results of the non-response analyses, performed at an early time point during the study, can be used as input for developing interventions to increase the participation rate later in the study. Effective participation enhancing strategies are useful when optimizing implementation of future prevention programs in primary care.

In comparable studies, including the pilot implementation of PC [14,15] the response rates were low, ranging from 3% to 75% [14,15,18]. Since this has been taken into account in the sample size calculation, sufficient power is expected even with low response rates. To enhance participation rates we plan to use several strategies, based on advise and results of previous studies [14] and on non-response analyses during the study. The accompanying information letter will emphasize safety in handling privacy sensitive data, especially digital data. Furthermore, the information letter will contain a short recap of the purpose of the letter and the advice to ask a family member for help with translation if considered necessary. The letter will present the recap in different languages. Reminder letters with a paper version of the risk estimation will be sent to all non-responders after two weeks. Furthermore, we evaluate a subgroup that is offered the possibility to bypass one of the GP consultations by ordering a toolbox. The toolbox is a tool that stimulates self-management; patients are able to take more responsibility for their own health. Furthermore, obtaining the additional measurements through a toolbox is easier to incorporate into ones busy life and this might enhance participation rates. A higher participation rate increases the cost-effectiveness of the entire program.

### Possible methodological threats

Several measures minimize possible bias in this study. To prevent selection bias, we aim at a representative sample for all GP practices in the Netherlands. Participating practices will be balanced in urban and rural locations and will have variable sizes, containing both solo and group practices. Selective participation can be an issue, since prevention programs sometimes tend to attract the patients referred to as the ‘worried-well’ [14,18,39]. However, the pilot implementation of the prevention program PC showed no presence of this effect [14,15]. The non-response analysis performed during study is sensitive to selection bias in case of low response rates and selective responders.

During this study participants are asked to report their own expenses and health care utilization, including consultations. Data collection by self-report can induce recall bias, but in combination with EMR data, we assume the outcome measures to be more reliable.

### Implementation challenges

Due to health care policy there is a possibility that changes in the health care environment will occur over time. For example, changes in established compensations for participation in prevention programs by health care insurers can influence the compliance and participation rates. However, these changes will occur in both the intervention groups and the waiting list control groups equally, so we expect this will not influence our study results.

### Conclusion

Prevention programs for CMD are an actual topic in health care. Under pressure of politics and society, implementation of these programs has already been initiated. Nevertheless, primary prevention of CMD by early risk factor modification has not yet been proven effective and cost-effective at population level. Before implementation on a large scale can be carried out, scientific support must be presented. If the INTEGRATE study shows PPA CMR to be effective and cost-effective, this will provide the evidence base that is needed for setting up prevention programs for CMD at national level. With determination of the profile of non-responders in prevention programs in primary care, the results of the INTEGRATE study will also assist in the development and implementation of similar prevention programs.

## Abbreviations

CMD: Cardiometabolic disease; EMR: Electronic medical record; GPs: General practitioners; HDL: High-density lipoprotein; ICER: Incremental cost-effectiveness ratio or incremental cost-utility ratio; ICPC: International classification of primary care; N: Number; PC: Preventive Consultation (Dutch: PreventieConsult CardioMetaboolRisico); PPA CMR: Personalized prevention approach for cardiometabolic risk; QALY: Quality-adjusted Life Years; RIVM-CDM: National Institute of Public Health and the Environment (RIVM) – Chronic Disease Model; SES: Socio-economic status.
